### Data Preparation

Data will be supplied in the format convenient for the original researchers. This project will take responsibility for converting, cleaning, and formatting the data as required before analysis. MEDAL and LUNA are data sets from previous funded studies and have been quality checked, analyzed, and published in peer-reviewed journals. Therefore, we will not assess the quality of the data, and we expect a limited need to clean them. Analyses of the BSGE data set have recently been published [22]. However, we will receive the raw source data, which will require cleaning, data quality checks, and assessment of the availability of relevant data for inclusion in the analysis. The collection of BSGE data is ongoing, so matching results from previous publications will be limited.

The 3 data sets (BSGE, MEDAL, and LUNA) will be employed when creating the prediction models, either as *development* or *external validation* data sets. To enable external validation of the prediction models, the predictors in the development data set will be matched with the variables in the validation data set. Where a direct match is not available in the data, we will investigate whether a new variable can be created from other information, such as calculating BMI from weight and height or categorizing continuous variables into groups.

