### Sample Size Considerations

This study uses pre-existing data sets to develop and validate multivariable prediction models, and at the outset of this project, no formal guidance on the minimum sample size was available. The available records from all 3 data sets will be used. However, for confirmation and after completing the analysis, we will compare our results with recently published recommendations for sample size calculations in prognostic studies [27].

The BSGE data set contains records of approximately 5000 women, of which approximately one-third are complete. Data availability for analysis is likely to increase with the selection of candidate factors from the list of available variables.

The MEDAL data set contains records of over 300 women, with approximately 110 confirmed diagnoses of endometriosis. We assume no impact of the additional diagnostic test (MRI) performed in one arm of the study and therefore include the full study population in our analyses. The analysis of treatment success in women with suspected endometriosis will examine a reduced set of candidate factors that are available before diagnostic laparoscopy. We will ensure that the list of factors considered is appropriate for the available sample size.

The LUNA data set will serve as an external validation set for the model developed to predict treatment success in women with suspected endometriosis. We will include both the treatment and control arms of the trial, as no evidence of an effect of the LUNA intervention was found for any of the pain outcomes included. The LUNA data set contains records of over 590 women, with approximately 140 women with confirmed endometriosis.

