### Model Development

A total of 2 groups of models will be developed, reflecting the 2 different populations of women we aim to study. The group of 5 primary models will predict treatment success in women with confirmed diagnoses according to the 5 outcomes described above. The second group will consist of 5 models that predict treatment success in women with suspected endometriosis. Overall, this will result in 10 distinct models.

For the primary models (for women with a confirmed diagnosis of endometriosis), we will use the BSGE data set; a randomly selected 10% of records will be removed for performance testing of the model. For the secondary models of women with suspected diagnoses, we will use the MEDAL data set. All models will be developed using a logistic regression approach, linking candidate factors to outcomes.

A backward selection process will be used to decide which of the candidate predictor variables should be included in the final models (with a cutoff value of *P*<.15 conservatively taken to warrant inclusion and prevent omission of important predictors); candidate factors will likely vary between the models.

Continuous variables will be kept as continuous in the models (and not dichotomized) to avoid loss of power. Nonlinear effects may be considered if allowed by the sample size. No imputation of missing data will be performed, but the missing data at random assumption will be investigated.

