## Discussion

### Principal Strengths

This protocol defines the methods that will be applied to develop and externally validate our clinical prediction models to predict which women will benefit most from laparoscopic surgery resulting in reduction of pain or increased QoL. Previous models have focused on directly predicting endometriosis in patients with chronic pelvic pain and other symptoms, with limited success, or restricted their models to limited patient populations, with limited generalizability.

Our approach will address some of the challenges that other researchers have faced when attempting to improve care for women with chronic pelvic pain and endometriosis. As the prediction models focus on patient-perceived outcomes (QoL and pain), they will be more clinically relevant to the patient, and we are not limited by the wide range of definitions and treatments specific to endometriosis diagnosis, which often prevents external validation. The use of pre-existing data allows a comparatively quick and efficient development of the model with no unknown quantities, such as attrition and data completeness.

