### Limitations

The use of pre-existing data collected as part of other projects means that we will be limited by the data as recorded and will have no input as to how and what information is collected. Nonetheless, we have been able to assess the extent of missing data and found it to be sufficiently low. Power considerations have been based on truly available data, and the large sample size, specifically in the BSGE data set, will allow us to investigate a wide range of prognostic factors.

A second limitation is the matching of variables in the development and external validation data sets. This challenge is common to many studies that use pre-existing external validation data sets. We have been comparing how data were collected in the data sets and found most variables to be compatible; however, not all factors that we may identify as prognostic will also be available in the validation data set, thereby limiting the list of prognostic factors that can be validated externally.

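### Imputation is ruled out although only about one third of BSGE records are complete, and the article's statements on missing data do not agree with one another

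*Protocol article*

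**What the plan says.** All places are in the protocol article.

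- **Model Development** sets the rule for all ten models: "No imputation of missing data will be performed, but the missing data at random assumption will be investigated". It does not say what follows if the assumption looks doubtful.
- **Sample Size Considerations** states: "The BSGE data set contains records of approximately 5000 women, of which approximately one-third are complete". It then adds: "Data availability for analysis is likely to increase with the selection of candidate factors from the list of available variables".
- **Data Preparation** says of the raw BSGE source data: "which will require cleaning, data quality checks, and assessment of the availability of relevant data for inclusion in the analysis".
- **Principal Strengths** presents the use of existing data as allowing quick development "with no unknown quantities, such as attrition and data completeness".
- **Limitations** says: "we have been able to assess the extent of missing data and found it to be sufficiently low". No figure or threshold is given.

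Three other statements matter here. Outcomes defines every outcome as a change from baseline to 6 months or 1 year, so each woman needs both a baseline and a follow-up score. The description of the data sets says BSGE holds pain and QoL before surgery and at 6, 12 and 24 months, and that collection continues. Model Performance and Internal Validation splits BSGE at random into 90% for development and 10% for validation.

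**The concern.** The no-imputation rule is a positive decision, not a detail left to an analysis plan. It is applied to a data set in which about two thirds of records are incomplete. Its only safeguard is to look into missing at random, which is not the condition that complete-case regression needs.

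The prediction tool is meant for all women like those in BSGE. If return of follow-up questionnaires is related to how well a woman did, coefficients and mean predicted change would be wrong for that population. The planned checks may not show this. The 10% hold-out is drawn from the same records under the same rule, so it shares any selection. External validation is in MEDAL, which the Table 1 footnote describes as absent or superficial disease, against deep disease in BSGE. Poor calibration there could not be attributed to missing data.

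The rule also discards information already collected. A woman without a 6-month score but with a 12- or 24-month score drops out of a 6-month model.

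Finally, a reader who relies on the Limitations section would not learn that most records in the main development set have gaps.

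**Working it through.** **Inputs.** About 5,000 BSGE records, of which a share *f* of about 1/3 is complete (Sample Size Considerations); a 90/10 split (Model Performance and Internal Validation). The article states no count of complete records, no power and no model-specific share, so there is no figure of its own to reproduce beyond the one third.

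**1. Usable records.** Complete = 5,000 × *f*; development = 0.9 × complete; hold-out = 0.1 × complete. Only *f* = 1/3 comes from the article. The other rows are an assumed range.

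| *f* | complete | dropped | development | hold-out |
|---|---|---|---|---|
| 0.30 | 1,500 | 3,500 | 1,350 | 150 |
| 1/3 | 1,667 | 3,333 | 1,500 | 167 |
| 0.50 | 2,500 | 2,500 | 2,250 | 250 |
| 0.80 | 4,000 | 1,000 | 3,600 | 400 |

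If all records were kept, the figures would be 4,500 and 500.

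**2. How far candidate selection could raise the share.** Assume independent and equal missingness over *k* variables, with one third of records complete over all of them. Then *m* selected variables are jointly complete in (1/3)^(*m*/*k*) of records.

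- 10 of 20: 0.58. 10 of 30: 0.69. 10 of 40: 0.76.
- 15 of 20: 0.44. 20 of 30: 0.48.

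The usable share could thus fall on either side of one half. If missing values cluster, as after a missed follow-up, the share rises much less. Dropping predictors cannot restore a missing follow-up score.

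**3. Precision.** Against a fully observed file, standard errors are up to √(5,000/1,667) = √3 = 1.73 times as large. This is an upper bound.

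**4. What investigating missing at random can deliver.** Observed data cannot separate missing at random from missing not at random. Nor is missing at random the relevant condition:

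- If missingness depends on the observed outcome or on variables outside the model, data can be missing at random while complete-case regression is biased. Imputation is then the valid choice.
- If a predictor is missing because of its own value, data are not missing at random, yet complete-case regression can be valid.

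So neither answer to the investigation settles whether deletion is acceptable.

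**5. Possible size of bias, on assumed inputs.** Simulated linear regression with 400,000 records, one standard normal predictor, outcome SD 1, R² of 0.1, 0.2 and 0.3, and one third of records retained by a logistic rule:

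| retention depends on | slope ÷ true slope | intercept shift (outcome SD) |
|---|---|---|
| nothing | 1.00–1.01 | about 0 |
| predictor (log-odds 0.7 per SD) | 0.99–1.01 | about 0 |
| outcome (0.7 per SD) | 0.91–0.94 | 0.31–0.39 |
| both (0.5 each) | 0.79–0.91 | 0.22–0.29 |

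The harm depends entirely on the mechanism, and the article does not describe one.

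**6. The statements side by side.** One third complete (Sample Size Considerations) does not fit an extent of missing data judged low enough (Limitations). An availability assessment still to be done on BSGE (Data Preparation) does not fit completeness as a settled quantity (Principal Strengths) or as already assessed (Limitations).

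**The case against.** The strongest reply is that one third describes whole records before candidate factors are chosen, and the article says so. Each primary model needs one outcome and its own predictors, not every field out to 24 months. Collection is also ongoing, so some incomplete records may belong to women who have not yet reached follow-up, which is not non-response. Even about 1,500 development records is a large sample, and complete-case regression is sound if missingness depends only on modelled predictors.

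Much of this stands, and it rules out three stronger readings.

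- A reader might infer that the primary models do rest on a selected minority of women. The documents do not support this: the model-specific share is not given and could exceed one half, and no outcome-related selection is shown.
- A reader might set the Principal Strengths remark against the one-third figure. That remark says completeness is known, not that it is high. Its conflict is with Data Preparation.
- A reader might take 1.73 as the precision that imputation would recover. It would not. Women without the outcome add little unless good auxiliary scores are observed for them, and the article does not say how many have these.

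The reply does not defend the rule itself. Expected improvement in availability is not quantified, every outcome still needs a follow-up score, and the Limitations statement carries no figure to support it.

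**Conclusion.** The point holds in this form. The article forbids imputation while reporting that about two thirds of its main development records are incomplete. The primary models may use as few as about 1,667 of 5,000 women, taking the one-third figure at face value; the true number for each model is unknown and may be higher. Complete-case analysis may turn out to be acceptable, but the article gives no argument that it is, and its only planned check addresses a different condition. Bias is possible, not demonstrated; the simulated sizes rest on assumed mechanisms and serve only to show that the question matters.

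Two internal conflicts need correction whatever method is chosen: Limitations against Sample Size Considerations, and Principal Strengths against Data Preparation.

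**What to change.** - **Method.** Replace the no-imputation rule with multiple imputation of predictors and outcome. Use baseline pain and QoL scores and the other follow-up scores as auxiliaries.
- **Scope.** Restrict imputation of a follow-up score to women who have reached that time point.
- **Hold-out.** Fit the imputation model separately in the 90% and 10% parts of BSGE, or otherwise ensure that nothing passes between them.
- **Sensitivity.** Keep complete-case analysis as a sensitivity analysis, and compare included with excluded women on baseline characteristics.
- **Reporting.** In Limitations, replace the general assurance with actual completeness per outcome and per candidate factor. Reword Principal Strengths so that it agrees with the assessment still planned under Data Preparation.

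**Cost.** No new data. The work is more than a few lines of code, because backward selection has to be run across imputed sets for each model. The stated quality of the data also becomes less favourable.

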### Model Performance and Internal Validation

After developing the models, we will assess how well they perform. Calibration will be assessed visually using scatter plots; the calibration slope will indicate whether predictions are systematically too high or low (calibration-in-the-large). The apparent performance of the final models will be evaluated in terms of discrimination using the C statistic.

As apparent performance is often optimistic (due to a model being developed and validated in the same data set), internal validation, which we refer to as model performance, will also be undertaken. For the primary models of treatment success in women with confirmed endometriosis, we will randomly divide the BSGE records into 2 data sets, development (90% of the data) and validation (10% of the data). The apparent performance of the models in the validation sample will be compared with their performance in the development data set. *Optimism* is the difference between the apparent value in the validation sample and the observed value in the development data set. This optimism estimate is then subtracted from the model’s apparent performance to obtain an optimism-adjusted estimate of each measure of performance for the model.

The sample size in the MEDAL data set is not sufficient to use the same approach for the secondary models of treatment success in women with suspected endometriosis. If deemed appropriate, we may implement a bootstrap resampling technique whereby the apparent performance of the developed model in bootstrap samples is compared with its performance in the model developed using the original data set.

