### Data Sets for Development of the Clinical Prediction Models

We have identified 3 suitable data sets that will be employed to develop and validate the clinical prediction models for women with confirmed and suspected diagnoses of endometriosis. We have guaranteed access to all three databases and data sharing agreements have been finalized *a priori*.

The British Society of Gynaecological Endoscopy (BSGE) maintains a national database that contains data of over 5000 women who had a confirmed diagnosis and underwent laparoscopic surgery for advanced endometriosis (stage 4). Records have been collected by clinicians at over 50 endometriosis centers in the United Kingdom since 2007 (data collection is ongoing). Endometriosis centers are commissioned by NHS England and accredited by the BSGE for complex multidisciplinary surgery required for the treatment of DE [19,20]. To maintain accreditation, the database serves as a mandatory record of DE cases and outcomes [21]. It includes data on patient characteristics, pain, and QoL before and 6, 12, and 24 months after surgery, along with intraoperative findings. It is the most comprehensive source of data on endometriosis surgery and QoL worldwide. Some of these data have recently been published [22].

The second data set comes from a clinical study of women with suspected endometriosis, specifically chronic pelvic pain. *MRI versus laparoscopy to diagnose the main causes of chronic pelvic pain in women: a test-accuracy study and economic evaluation* (MRI to establish diagnosis against laparoscopy [MEDAL]) [ISRCTN13028601], was a comparative test-accuracy study assessing whether magnetic resonance imaging (MRI) could replace or triage the use of laparoscopy in establishing a diagnosis among women presenting in secondary care with chronic pelvic pain. Data were collected on patient characteristics, pain, and QoL before and after diagnostic laparoscopy with or without surgery, along with intraoperative findings for over 300 women who underwent laparoscopic surgery for chronic pelvic pain at 26 UK hospitals. During surgery, over a third of the women were diagnosed with endometriosis [23].

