**External validation**		
	MEDAL data set	Laparoscopic uterosacral nerve ablation (control arm only)

^a^Databases containing pre-, intra-, and postoperative information of women with deep endometriosis (British Society of Gynaecological Endoscopy) or absent or superficial endometriosis (magnetic resonance imaging to establish diagnosis against laparoscopy or laparoscopic uterosacral nerve ablation).

^b^BSGE: British Society of Gynaecological Endoscopy.

^c^MEDAL: magnetic resonance imaging to establish diagnosis against laparoscopy.

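### One random 90/10 split of BSGE records wastes data and leaves the primary models untested in an unseen center treating deep endometriosis

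*Protocol article*

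**What the plan says.** The split is fixed in three places of the protocol article.

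- Model Development: "a randomly selected 10% of records will be removed for performance testing of the model".
- Model Performance and Internal Validation: "we will randomly divide the BSGE records into 2 data sets, development (90% of the data) and validation (10% of the data").
- Table 1 assigns a random 90% of BSGE to development and the remaining 10% to model performance.

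On the source of the data, the section on data sets says: "Records have been collected by clinicians at over 50 endometriosis centers in the United Kingdom since 2007". None of the three places groups or stratifies the split by center.

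On size, Sample Size Considerations says: "The BSGE data set contains records of approximately 5000 women, of which approximately one-third are complete". It adds: "Data availability for analysis is likely to increase with the selection of candidate factors from the list of available variables". Model Development rules out filling the gaps: "No imputation of missing data will be performed, but the missing data at random assumption will be investigated".

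External Validation and Recalibration sends the primary models to MEDAL. Footnote a of Table 1 contrasts the populations, setting "women with deep endometriosis (British Society of Gynaecological Endoscopy) or absent or superficial endometriosis", the latter being MEDAL and LUNA.

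**The concern.** Internal validation should show how much performance is lost when the model meets women who did not shape it. Here the held-out women come from the same centers, surgeons and recording habits as the development women. The split can expose some overfitting to individual records, but not a drop in performance from one center to the next.

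Three things are at stake:

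- The performance estimate is imprecise because it rests on a tenth of the usable records.
- The model itself is built on nine-tenths of them.
- The article offers the finished models for general clinical use, yet no step shows how the primary models behave in a specialist center that did not contribute to them. BSGE is the only one of the three data sets described as deep disease, so that question can be answered only across BSGE centers.

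**Working it through.** The article gives no precision or power figure for the internal validation, so there is no stated number to reproduce.

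**Inputs from the protocol article.** About 5000 BSGE records, about one-third complete; over 50 centers (50 used below); 10% held out; no imputation; MEDAL with about 110 confirmed cases at 26 hospitals.

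**Assumptions.** R2 of 0.1 to 0.3, because none is given. Women are treated as independent, so every half-width below is a lower bound if outcomes cluster by center. The slope formula is for a continuous outcome, which is what the Outcomes section specifies. (Model Development names logistic regression and the Abstract linear regression.)

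**1. Size of the held-out set.**
- Low end: 5000/3 ≈ 1667 usable; 0.10 × 1667 ≈ 167 held out, about 1500 for development. Per center: 167/50 ≈ 3.
- High end: 5000 usable; 500 held out, 4500 for development. Per center: 10.

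**2. Does the held-out set contain new centers?** A center with m usable records has none in development with probability of about 0.1^m. For m = 3 this is 0.001. At the low-end average of m = 1667/50 ≈ 33 it is about 10^-33. In a simulation of 50 centers with skewed sizes, 0.15% of held-out women came from a center unseen in development with 1667 records, and 0.02% with 5000.

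**3. Precision of the calibration slope.** SE = sqrt((1 − R2)/(R2 × n)); 95% half-width = 1.96 × SE. For R2 = 0.2 and n = 167: 1.96 × sqrt(0.8/(0.2 × 167)) = 0.30.

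| Assumed R2 | n = 167 (10% of 1667) | n = 500 (10% of 5000) | n = 1667 (all) | n = 5000 (all) |
|---|---|---|---|---|
| 0.1 | 0.46 | 0.26 | 0.14 | 0.08 |
| 0.2 | 0.30 | 0.18 | 0.10 | 0.06 |
| 0.3 | 0.23 | 0.13 | 0.07 | 0.04 |

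The ratio between using 10% and using all records is sqrt(10) ≈ 3.2 throughout.

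**4. The same check on the C statistic.** By the Hanley-McNeil formula, with an assumed C of 0.70 and 75% successes, the half-width is 0.085 at n = 167 and 0.049 at n = 500, against 0.027 at n = 1667 and 0.015 at n = 5000.

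**5. What MEDAL adds.** With 110 confirmed cases, all usable, the slope half-width at R2 = 0.2 is 1.96 × sqrt(4/110) = 0.37. If performance falls there, a difference between hospitals cannot be separated from a difference in disease.

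**6. Can single centers be left out?** With about 33 complete records in a center, the half-width at R2 = 0.2 is 1.96 × sqrt(4/33) = 0.68, which is too wide to read alone. Ten groups of five centers would hold about 167 women each, with a half-width of 0.30 per group, while the pooled estimate uses all 1667.

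**The case against.** The best defence is that the split is labelled internal validation and is meant to measure optimism; testing in a new setting is a separate, planned step. This stands in part. A reader might infer that the primary models are never tried in a new hospital. The article does not support that: MEDAL is an external test at 26 hospitals, with recalibration or revision foreseen if performance is poor. What remains is the narrower gap of an unseen center treating deep disease. Even that relies on the general description in Table 1 footnote a, since no stage breakdown of MEDAL is given.

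Second, 167 is a floor. The article expects more usable records once the candidate factors are chosen, so the fair statement is a range of 167 to 500.

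Third, the half-widths for all records ignore clustering and so flatter the alternative somewhat.

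A reader might also infer that the models ignore correlation within centers, so that selection at P<.15 keeps predictors too easily. The article does not establish this. It says "All models will be developed using a logistic regression approach, linking candidate factors to outcomes" and is silent on error structure, a detail that an unshown analysis plan may hold. The familiar design effect, 1 + (m − 1) × ICC, applies to predictors constant within a center, and no such candidate is named. For a factor varying within centers, with both ICCs assumed at 0.05, inflation is only about 1 + 32 × 0.05 × 0.05 = 1.08. This part is not raised as an error.

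**Conclusion.** The point stands for the split itself, which the article fixes outright; center terms added in an analysis plan would not repair it. The internal performance of the primary models will rest on about 167 to 500 women from centers already represented in development. At R2 = 0.2 the calibration slope is known only to about ±0.30 to ±0.18, where all records would give about ±0.10 to ±0.06 before clustering. At the low end, an interval of roughly 0.7 to 1.3 around a slope of 1 cannot separate good calibration from material overfitting. Performance in an unseen center treating deep endometriosis is not estimated at any step.

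The sizes depend on the assumed R2, on 50 centers and on how many records prove usable. The threefold loss of precision against using all records does not depend on R2 or on the usable number, but it does assume independent women. This is an inefficient and incomplete method that should be replaced, not a contradiction in the plan.

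**What to change.** In Model Development, Model Performance and Internal Validation, and Table 1:

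- Develop the primary models on all usable BSGE records.
- Replace the split with internal-external cross-validation that leaves out one group of centers at a time, repeating the backward selection in each fold.
- Report the pooled calibration slope and intercept and their spread across center groups, read against the sampling error of each group.
- If the pseudonymized extract has no center identifier (the article does not say), use a bootstrap optimism correction that repeats the selection in every sample. The article already considers a bootstrap for the secondary models. This recovers the lost data but does not test new centers.
- Optionally, use a center random intercept or cluster-robust standard errors in the selection step.

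The cost is modest programming and no new data collection. Reported performance may look slightly less favourable. The article says analysis was already under way, so models already fitted on the 90% would need refitting and the change should be recorded.
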